## Abstract

**Introduction:**

Acute myeloid leukemia (AML) has a dismal prognosis, mostly due to minimal residual disease-driven relapse, making an elimination of persisting therapy-resistant leukemia progenitor/stem cells (LPCs) the main goal for novel therapies. Peptide-based immunotherapy offers a low-side-effect approach aiming to induce T cell responses directed against human leukocyte antigen (HLA) presented tumor antigens on malignant cells by therapeutic vaccination. Mass spectrometry-based analysis of the naturally presented immunopeptidome of primary enriched LPC and AML samples enabled the selection of antigens exclusively expressed on LPC/AML cells, which showed *de novo* induction and spontaneous memory T cell responses in AML patients, and whose presentation and memory T cell recognition was associated with improved disease outcome.

**Methods:**

Based on these data the therapeutic vaccine AML-VAC-XS15 was designed, comprising two mutated HLA class I-restricted peptides from the common AML-specific mutation in NPM1 and seven HLA class II-restricted peptides (six non-mutated high-frequent AML/LPC-associated antigens and one mutated peptide from the AML-specific mutation R140Q in IDH2), adjuvanted with the toll like receptor 1/2 ligand XS15 and emulsified in Montanide ISA 51 VG. A phase I open label clinical trial investigating AML-VAC-XS15 was designed, recruiting AML patients in complete cytological remission (CR) or CR with incomplete blood count recovery. Patients are vaccinated twice with a six-week interval, with an optional booster vaccination four months after 2nd vaccination, and are then followed up for two years. The trial’s primary objectives are the assessment of the vaccine’s immunogenicity, safety and toxicity, secondary objectives include characterization of vaccine-induced T cell responses and assessment of preliminary clinical efficacy.

**Ethics and dissemination:**

The AML-VAC-XS15-01 study was approved by the Ethics Committee of the Bavarian State medical association and the Paul-Ehrlich Institut (P01392). Clinical trial results will be published in peer-reviewed journals.

## Introduction

1

Acute myeloid leukemia (AML), a malignant disorder of the bone marrow characterized by the clonal expansion and differentiation arrest of myeloid progenitor cells (1), is the most common form of acute leukemia in adults, yet shows the worst outcome of all leukemias with a 5-year survival rate of only 30% (2). Despite numerous treatment advances in recent years and high initial remission rates, disease relapse occurs in a large proportion of patients, resulting in the still very high mortality rate of AML (3). Most treatment advances that were achieved over the last decades have mainly led to a benefit for younger patients, as they tend to be based on intensive chemotherapy and the increased use of allogeneic stem cell transplantation. Moreover, attempts to find treatment strategies based on the increasing knowledge on the molecular subgroups of AML have led to the approval of a number of new substances like enasidenib, ivosidenib or gilteritinib. However, none of them have so far shown a significant impact on overall survival (4). The prognosis for medically unfit patients and patients above the age of seventy remains dismal due to their ineligibility for intensive treatment and the resulting high relapse rates (5, 6). The main reason for disease relapse is the presence of minimal residual disease (MRD), which is characterized by the persistence of therapy-resistant leukemia stem and progenitor cells (LPCs) in the patients’ bone marrow (7). To eliminate these cells and achieve long-lasting remissions and potential cure, the development of novel therapeutic approaches that specifically target these residual cells is urgently needed.

One option to achieve this goal is T cell-based immunotherapy, which harnesses the immune system to eliminate malignant cells. The immunogenicity of AML, which is documented by graft-versus-leukemia effects after hematopoietic stem cell transplantation (8) as well as the favorable immune effector-to-target cell ratios in the MRD setting, suggests that AML might be effectively targeted by T cell-based immunotherapy (9). In recent years, the breakthrough clinical success of T cell-based immunotherapy approaches, including immune checkpoint inhibitors, chimeric antigen receptor T cells, bispecific antibodies and adoptive T cell transfer, have revolutionized the treatment of many malignant diseases (10–12). However, the majority of patients and cancer entities, including AML, still do not benefit from available immunotherapeutic strategies, others for a limited time only (13–16). Remaining challenges to augment the efficacy of T cell-based immunotherapy are therefore to improve specificity of treatment, to increase the frequency of anti-tumor immune responses, as well as to reduce toxicity and to expand the spectrum of targetable cancer entities. A rational and promising low side-effect approach to achieve this goal is peptide-based immunotherapy (17, 18), which aims to induce a T cell response directed against tumor antigens (TAs), presented on the surface of tumor cells via human leukocyte antigen (HLA) molecules, by using therapeutic vaccination (19). These TAs can arise from tumor-specific mutations or from non-mutated, differentially expressed and presented gene and protein products in the tumor cell (19).

For the development of novel immunotherapeutic approaches for AML, the specific therapeutic targeting of the relapse-inducing LPC subpopulation is of central importance. To identify widely applicable and naturally presented LPC antigens, we used a well-established mass spectrometry-based immunopeptidomics workflow within a large cohort of primary AML samples (taken from patients at first diagnosis as well as in a relapse situation), to identify frequent HLA class I- and HLA class II-restricted antigenic peptides presented exclusively on the CD34^+^CD38^-^ LPC subpopulation or on both LPCs and AML blasts (20). By comparative immunopeptidome profiling using a large and diverse benign immunopeptidome database (20–22), antigens were selected based on their frequent and exclusive presentation within the AML cohort, with no detection on any benign tissue of hematologic or non-hematologic origin (23). Additionally, screening of the AML/LPC immunopeptidomes for peptides derived from common AML-specific mutations (*e.g.* FLT3, NPM1, IDH2, DNMT3A) enabled the identification of naturally presented neoepitopes of NPM1 and IDH2. Functional characterization of these novel mutated and non-mutated AML/LPC antigen targets showed *de novo* induction and spontaneous memory T cell responses in samples of AML patients and healthy volunteers (23). Of note, it was further shown that a diverse presentation of these AML-exclusive antigens is associated with an improved disease outcome in AML patients (23), highlighting the clinical relevance of these antigens.

Based on these analyses, an AML/LPC peptide vaccine was designed, comprising nine mutated and non-mutated AML- and AML/LPC-associated HLA class I and HLA class II-restricted peptides. As an adjuvant our toll like receptor (TLR) 1/2 agonist XS15 (24) emulsified in Montanide ISA 51 VG was chosen, which has already been used in several clinical trials (25–27), showing a beneficial safety profile as well as the induction of strong and long-lasting T cell responses even in immunocompromised cancer patients (19, 25, 26, 28). The first-in-human (FIH) study described here has been designed in accordance with the recommendations of the SPIRIT 2013 Statement (29) to evaluate the resulting multi-peptide vaccine AML-VAC-XS15, with regard to overall safety and tolerability, as well as first signs of clinical efficacy in AML patients.

## Materials

2

The vaccine AML-VAC-XS15 evaluated in this trial consists of nine AML-specific peptides, the adjuvant XS15 and the emulsifier Montanide ISA 51 VG (**Figure 1**). The peptide mixture contains 300 µg each of one AML-specific mutated (R140Q in IDH2) peptide and six immunopeptidome-defined non-mutated AML- and LPC-associated HLA class II-restricted peptides with promiscuous binding to multiple HLA class II allotypes, as well as 300 µg each of two immunopeptidome-defined mutation-derived AML-associated HLA class I-restricted neoepitopes from the common AML-specific mutation in NPM1. All peptides were selected from a collection of AML- and AML/LPC-associated antigens characterized on primary AML blasts and LPCs by direct isolation of naturally presented HLA class I and HLA class II ligands from leukemia cells and subsequent identification via mass spectrometry. The peptides had been functionally characterized regarding their ability to induce T cell responses and their clinical relevance (23).

**Figure 1 f1:**
[figure not shown]
Construction of the vaccine. After an extensive comparison of immunopeptidomes of acute myeloid leukemia (AML) cells (red), leukemia stem and progenitor cells (LPC) (blue) and benign tissue cells (green), the LPC/AML non-benign overlap (red-black hatched) was isolated and used to provide six human leukocyte antigen (HLA) class II-restricted non-mutated (blue dots), one HLA class II-restricted mutated (green dot) and two HLA class I-restricted mutated (yellow dots) peptides for the peptide mix, including the adjuvant XS15. The peptide mix is emulsified with Montanide ISA 51 VG to formulate the multi-peptide vaccine.

The lipopeptide XS15, chemical name N-Palmitoyl-S-[2,3-bis(palmitoyloxy)-(2R)-propyl]-Icysteinyl-GDPKHPKSF, is a water-soluble synthetic Pam3Cys-derivative. Due to its function as TLR1/2 ligand, it was chosen as a suitable adjuvant to complement the peptide cocktail in the AML-VAC-XS15-01 trial. Peptide mix and 0.12 mg XS15 are reconstituted in 33% dimethyl sulfoxide (DMSO)/water for injection.

Prior to application, the cocktail of AML-associated peptides and XS15 is emulgated in a water-oil emulsion 1:1 with Montanide ISA 51 VG. Montanide ISA 51 VG is based on a blend of mannide monooleate surfactant and mineral oil, has been used as an adjuvant in more than 200 human vaccine trials and renders stable water-in-oil emulsions when mixed with water-based antigenic media.

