### Study design

3.2

Trial duration will be approximately 26 months for each patient, however, the actual treatment phase will cover only 1.5 months (**Figure 3**). During that time, patients will receive two vaccine doses of AML-VAC-15, six weeks apart, administered subcutaneously into the skin of the lower abdomen. If an insufficient T cell response is measured four weeks after the second vaccination, a booster vaccination may be applied four months after the second vaccination, which will then be followed up with an extra safety visit four weeks later. This particular dosing scheme is based on results of our previous vaccination trials in healthy adults (P-pVAC-SARS-CoV-2, NCT04546841) (25), cancer patients with B cell/antibody deficiency (B-pVAC-SARS-CoV-2, NCT04954469) (26), glioblastoma patients (GLIO-XS15, NCT04842513) and patients with chronic lymphocytic leukemia (CLL) (XS15-iVAC-CLL01, NCT02802943). Data available from those studies so far shows that the dose of 300 µg per peptide adjuvanted with the TLR1/2 ligand XS15 (50 µg) emulsified 1:1 in Montanide ISA 51 VG is safe and effective to induce profound and long lasting CD4^+^ and CD8^+^ T cell responses that by far exceed those induced by previous peptide vaccines as well as by mRNA-based vaccines (25, 26). Therefore, to balance minimal side effects with maximum immune response induction, two vaccinations spaced six weeks apart are applied within the trial, with the option of a booster for those patients whose T cell responses are still insufficient after two vaccinations.

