### Statistical considerations

3.4

According to usual practice in early phase I studies, statistical planning is designed so that a statistically reasoned decision regarding a subsequent phase II study (for or against) can be made. The trial’s sample size was chosen based on the assumption that, in case of the induction of a peptide-specific immune response in ≤ 30% of patients the therapeutic concept will be extended with a probability of at most 5% (type one error, one-sided). Contrastingly, in case of the induction of a peptide-specific immune response in ≥ 60% of patients, the therapeutic concept should be followed with a probability of at least 80% (power). Given a sample size of n = 20 patients, this entails that at least 10 patients must show an immune response for the therapeutic concept to be evaluated in a phase II study. The exact power is 87%, the exact type 1 error is 4.8% (with calculations based on the binomial distribution with n = 20, p = 0.3 or p = 0.6, k < 10 or k ≥ 10).

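### The XS15 amount prepared for this trial (0.12 mg) and the amount in the dose rationale (50 µg) differ 2.4-fold, and the protocol does not explain the difference

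*Protocol article*

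**What the plan says.** Three statements in the protocol article bear on the point.

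- **Section 2 (Materials), peptides:** "The peptide mixture contains 300 µg each of one AML-specific mutated (R140Q in IDH2) peptide". The same sentence gives the same amount for the other eight peptides.
- **Section 2 (Materials), adjuvant, in the text after the Figure 1 caption:** "Peptide mix and 0.12 mg XS15 are reconstituted in 33% dimethyl sulfoxide (DMSO)/water for injection". The product is then emulsified 1:1 with Montanide ISA 51 VG.
- **Section 3.2 (Study design):** "This particular dosing scheme is based on results of our previous vaccination trials in healthy adults", followed by three further patient groups. The section then says that the data from those studies show "the dose of 300 µg per peptide adjuvanted with the TLR1/2 ligand XS15 (50 µg) emulsified 1:1 in Montanide ISA 51 VG" to be safe and effective at inducing T cell responses. It draws this trial's two-dose schedule with optional booster from that evidence.

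The article gives no injected volume, withdrawn fraction or fill excess. It does not say that the XS15 amount in this trial differs from that of the earlier trials.

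**The concern.** Section 3.2 carries the dose justification. It argues from a specific combination of peptide amount, adjuvant amount and emulsifier ratio in earlier trials to the regimen used here. Two of the three elements match the product described in section 2. The third, XS15, does not, and nothing in the text acknowledges it.

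A reader who follows section 2 as written would conclude that each vaccination combines 300 µg of every peptide with 120 µg XS15. The 50 µg experience cited in section 3.2 does not cover that combination. If the injected amount is instead the one in section 3.2, section 2 gives a misleading picture of the composition.

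Safety and immunogenicity are the two primary objectives (section 4), and the Discussion (section 5) also leans on earlier XS15 trials for tolerability and T cell potency. Readers of the results need to know which adjuvant amount they refer to, and whether the cited experience is at that amount.

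**Working it through.** **Background check.** The only computed design figures in the article are in section 3.4 (Statistical considerations): "The exact power is 87%, the exact type 1 error is 4.8" per cent. With n = 20 and success at 10 or more responders, the exact binomial gives:

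- P(X ≥ 10 | p = 0.3) = 0.0480
- P(X ≥ 10 | p = 0.6) = 0.8725

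Both agree with the stated values. Neither uses the adjuvant amount, so this point leaves them untouched.

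**Inputs for the point itself**

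| Quantity | Section 2 (this trial's product) | Section 3.2 (earlier trials, used as rationale) |
|---|---|---|
| Each peptide | 300 µg | 300 µg |
| XS15 | 0.12 mg | 50 µg |
| Emulsification with Montanide | 1:1 | 1:1 |

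**Step 1, units and ratio.** 0.12 mg × 1000 = 120 µg, and 120/50 = 2.4. The ratio of each peptide to XS15 is 300/120 = 2.5 in section 2 and 300/50 = 6 in section 3.2.

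**Step 2, could only part of one mixed preparation be injected?** Assume the peptides and XS15 are in one solution holding 300 µg of each peptide and 120 µg XS15.

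- To deliver 50 µg XS15, the fraction injected is 50/120 = 0.417. Each peptide then comes to 300 × 50/120 = 125 µg, not 300 µg.
- To deliver 300 µg of each peptide, the whole preparation is injected, and XS15 is 120 µg, not 50 µg.

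Under this assumption no single fraction gives both figures of section 3.2.

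**Step 3, could the 1:1 emulsification explain it?** No. Emulsifying lowers the concentration but leaves the total amount unchanged. Even a mistaken halving would give 120/2 = 60 µg, not 50 µg.

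**Step 4, what could explain it?** Either of two arrangements would.

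- XS15 comes in its own container with an excess, and only part of it is used. The peptide amount is then independent of the 0.12 mg.
- The 300 µg is the delivered amount and 0.12 mg is the content of the preparation. Delivering 300 µg with 50 µg XS15 from one mixed preparation would then require it to contain 300 × 120/50 = 720 µg of each peptide.

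The article states neither. Its wording on the container is not decisive: the sentence on reconstitution names the peptide mix and XS15 as two items, while the Figure 1 caption describes the adjuvant as part of the peptide mix.

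**The case against.** The strongest reply is that the two sentences describe different things. Section 2 gives an amount reconstituted during preparation, and section 3.2 gives a dose attributed to earlier trials. Neither states the XS15 amount injected per vaccination in this trial. Volumes, fill excess and withdrawal instructions normally sit in the full protocol or pharmacy documents, which are not shown. Section 3.2 can also be read as mainly justifying the schedule.

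Much of this stands. Step 2 excludes proportional withdrawal from one mixed preparation and does not exclude overfill in general. The absence of a withdrawal volume from an article is not itself a fault.

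What remains is that section 3.2 cites a particular XS15 amount as evidence for this trial's dosing, while section 2 states another for this trial's product. The peptide amount is identical in both, and no word connects the two XS15 figures. That is an unexplained discrepancy between two stated amounts, which goes beyond an omitted detail.

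A reader might go further and infer that patients receive 2.4 times the adjuvant dose supported by earlier trials. The documents do not support that, because they do not show what is injected. The first-in-human label should not add to the alarm either. It appears in "The first-in-human (FIH) study described here has been designed in accordance with the recommendations of the SPIRIT 2013 Statement", where it concerns the multi-peptide vaccine, and the Introduction says just before this that the XS15/Montanide adjuvant has already been used in several trials.

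**Conclusion.** The point holds as a consistency issue. The XS15 amount prepared for this trial and the amount in the dose rationale differ by a factor of 2.4, with no explanation, while the other stated elements of the formulation agree. It is not an arithmetic error in the design, and the decision rule, sample size, type 1 error and power stand.

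The consequence is conditional:

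- **If 120 µg is injected,** the 50 µg experience in section 3.2 does not cover the amount given, and the rationale needs restating. This would apply to all 20 patients: 20 × 2 = 40 injections if all receive both doses, and up to 20 × 3 = 60 if every patient is boosted.
- **If 0.12 mg is only a prepared amount and 50 µg is injected,** the trial is unchanged and the fault lies in the text alone.

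The documents do not show which applies, and I take no position on which figure is right. The finding that partial injection fails rests on the peptides and XS15 being drawn up in the same proportion, with 300 µg as the content. The discrepancy between the two sections does not depend on that assumption.

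**What to change.** Reconcile section 2 and section 3.2 against the product file:

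1. State whether 0.12 mg XS15 is a prepared or an injected amount.
2. Give the matching peptide amounts on the same basis, so that 300 µg is clearly either content or delivered amount.
3. If the injected XS15 amount differs from that of the cited earlier trials, say so and restate the dose rationale. If it does not differ, correct or explain the sentence in section 2.

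The cost is one check of the product file and one or two sentences of text. No change to the statistical design is needed.

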## Methods

3

### Participants

3.1

The trial enrolls 20 AML patients who have achieved complete remission (CR) or CR with incomplete blood count recovery (CRi) with first line therapy and are not eligible for an allogeneic stem cell transplantation (**Figure 2**). This includes AML patients who will continue to receive low-dose or maintenance therapy during the trial, with ongoing therapy being coordinated by the primary responsible oncologist. Patients must have achieved cytological CR/CRi but may be MRD positive or negative. By defining the study population in this fashion, adult patients from all age and fitness categories may be included, independent of risk classification or ongoing therapy. Only patients who are eligible for allogeneic stem cell transplantation are excluded, as in the course of an allogeneic stem cell transplantation the complete T cell compartment is replaced by the donor’s immune system. T cells of the patient are specifically destroyed as part of graft rejection and GvHD prophylaxis, T cells induced by the trial vaccine will thus be eliminated and replaced by donor cells without any effect of the vaccination being expected to remain. There will be no healthy control subjects in the study. Detailed inclusion and exclusion criteria are therefore as follows:

**Figure 2 f2:**
[figure not shown]
Study population within the framework of current treatment guidelines of the medical societies in hematology and medical oncology of the German speaking countries (DGHO) (4). Study patients must have reached complete remission (CR) or CR with incomplete blood count recovery (CRi) with any type of first-line therapy. Allogeneic stem cell transplantation (allo-Tx) must not be a viable treatment option. AML, acute myeloid leukemia; APL, acute promyelocyte leukemia; 7 + 3, combinatorial treatment with cytarabine (7 days) and daunorubicin (3 days); CBF, core binding factor mutation; GO, gemtuzumab ozogamicin; mut, mutated; sAML, secondary AML; tAML, therapy-associated AML; LDAC, low-dose cytarabine; IDAC, intermediate-dose cytarabine; HDAC, high-dose cytarabine; CC-486, oral azacytidine; CPX-352, liposomal cytarabine and daunorubicin; HMA, hypomethylating agent.

Inclusion criteria

Ability to understand and willingness to sign a written informed consent document.Males or females aged ≥ 18 years of age.Documented diagnosis of AML according to WHO guidelines.o Morphological CR or CRi, positive MRD is permitted.o Completion of previous intensive therapy (first vaccination 4-28 weeks after last application of intensive chemotherapy).o Ongoing low intensity treatment, e.g. with hypomethylating agents (HMA) and venetoclax, is permitted.o Ongoing maintenance treatment, e.g. with oral azacytidine or midostaurin, is permitted.o Not eligible for allogeneic stem cell transplantation.Eastern Cooperative Oncology Group (ECOG) performance status score of ≤ 2.Adequate organ function laboratory values.o Bilirubin ≤ 3 times upper limit range [exception isolated indirect hyperbilirubinemia (Morbus Gilbert-Meulengracht)].o Alanine aminotransferase and aminotransferase, ≤ 5 times upper limit range.o Creatinine clearance > 30 ml/min (according to Chronic Kidney Disease Epidemiology Collaboration formula).o Platelets > 50.000/μl.o Absolute CD3^+^ T cell count ≥ 200/μl.Negative serological Hepatitis B test or negative PCR in case of positive serological test without evidence of an active infection, negative testing of Hepatitis C RNA, negative HIV test within 6 weeks prior to study inclusion.Female patients of childbearing potential and male patients with partners of childbearing potential, who are sexually active, must agree to the use of two effective forms (at least one highly effective method) of contraception. This should be started from the signing of the informed consent and be continued until 3 months (both female and male patients) after last vaccination).For female patients of childbearing potential two negative pregnancy tests (sensitivity of at least 25 U/mL) prior to first vaccination, one at screening and the other prior (< 24 h) to first vaccination.Postmenopausal or evidence of non-child-bearing status.

Exclusion criteria

Pregnant or breastfeeding.Unwilling or unable to follow the study schedule for any reason.Chemotherapy or other systemic therapy or radiotherapy, up to 14 days prior to the first dose of study drug (ongoing low intensity or maintenance treatment with e.g. HMA, venetoclax or midostaurin is permitted).Concurrent or previous treatment within 28 days in another interventional clinical trial with an investigational anticancer therapy or any other investigational therapy, which would interfere with the study’s primary and secondary endpoints.Major surgery within 28 days of dosing of study drug.Treatment with immunotherapy agents within 28 days of dosing of study drug.Diagnosis of acute promyelocytic leukemia (APL).Autoimmune disease that requires or has required treatment with systemic immunosuppressive treatments, except low dose corticosteroids (< 10 mg/day), in the past 1 year.Prior history of malignancies, other than AML/myelodysplastic syndrome (MDS), unless the subject has been free of the disease for ≥ 5 years. Exceptions include the following: basal cell carcinoma of the skin, carcinoma *in situ* of the cervix, carcinoma *in situ* of the breast, histological finding of prostate cancer of TNM stage T1.Prior stem cell allograft.Ongoing or active infection (including SARS-CoV-2).Any live vaccination within 28 days prior to the first dose of the study drug.Known hypersensitivity against components of the vaccine.

